# Statistical Considerations

## Study Outcome Measures and Analysis

The primary outcome for the clinical part of the study will be cure rates in arms 1 and 3. Cure rates will be analyzed separately for Day 28 and 42.

The primary outcome of this study is a nominal variable: the treatment will be characterized as successful or unsuccessful/resistant. Cure rates will be summarized along with 95% confidence intervals (exact based on binomial distribution). The resulting categorical frequency data between arm 1 and 3 will be compared in Chi2-tests.

The secondary endpoints of this study are continuous variables. Overall group differences between secondary endpoints of parasite clearance time (PCT), gametocyte clearance time (GCT), and fever clearance time (FCT) will be compared using the Mann-Whitney U test. In vitro data will be analyzed by nonlinear regression models. The alpha level for tests used to compare differences between treatment groups will be 5%.

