# Background Information and Scientific Rationale

## Background Information

In 2006/2007 we conducted the ARC1 study (Artemisinin Resistance in Cambodia 1, WRAIR #1296, HSRRB A-13922), which used an integrated *in vivo – in vitro* approach with the aim of investigating reports of emerging artemisinin resistance in Cambodian patients with uncomplicated falciparum malaria. Preliminary data from this study suggest that along parts of the Cambodian-Thai border there are individual *P. falciparum* isolates, which are be highly resistant to artemisinins. Although the prevalence of these isolates was low, the overall sensitivity of the parasite isolates was significantly reduced as compared to western Thailand, an area with relatively high levels of antimalarial drug resistance, but at the same time an area from which so far there are no reports of increased numbers of failures with artemisinin-based combination therapies (ACTs). In ARC1 some individual isolates were associated with greatly increased parasite clearance times, treatment failures despite 7 days of artesunate monotherapy (4mg/kg), and very high inhibitory concentrations for artemisinins *in vitro*.

In that study the 28-day cure rate in the 4 mg/Kg/Day X 7 days artesunate monotherapy arm (n=60) was 93.3 % (95% CI: 83.8-98.2) vs. 100% (89.7-100%) in the control group (quinine – tetracycline for 7 days following the national treatment guidelines in Cambodia). Mean PCT in the 4 patients who failed artesunate monotherapy was almost twice that of those who were cured (97.6 vs. 52.2 hrs). *In vitro* drug susceptibility tests indicate significantly higher geometric mean IC50s for artemisinins as compared to western Thailand and Bangladesh. Patients who failed therapy had IC50 values up to 5 times higher than the overall mean. Drug levels measured 90 and 150 minutes after drug intake on day 0 were used to define individual DHA levels. Of the 4 patients who failed therapy, two had satisfactory drug levels while the other two did not. Although some failures may therefore be linked to inadequate drug levels, at least 2 patients (3.3%; 95% CI: 0.4-11.5) with the highest artemisinin IC50s and PCTs of 133 and 95 hrs failed therapy in spite of adequate drug levels suggesting clinically significant resistance to artemisinins.

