# Objectives

**3.1 PRIMARY OBJECTIVE:**

- The principal aim of this project is to determine the role of varying doses of artesunate for treatment outcome and whether higher doses of artesunate could overcome the problem of reduced artemisinin sensitivity in the region.
- To determine the safety and tolerability of this previously untested experimental high dose (6 mg/Kg/D X 7 day, total 42 mg/Kg) artesunate monotherapy regimen.

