# Study Design

This is an open label, randomized study. The study design is largely based on the WHO recommendations for the ‘Assessment and Monitoring of Antimalarial Drug Efficacy for the Treatment of Uncomplicated Falciparum Malaria’ (WHO, 2003). Patients with acute uncomplicated falciparum malaria will be randomly enrolled in 3 arms: All patients in arm 1, 2, and 3 will receive artesunate monotherapy for 7 days (Table 7). The ratio of enrollment into the 3 groups will be 2:1:2. Arm 2 serves as a control and will serve as a bridge to the ARC 1 study performed in 2006/2007. Patients in Arm 1 will receive a relatively low “standard” dose, and patients in Arm 2 will receive the intermediate dose of 4 mg/kg that was used in the ARC1 study. Patients in Arm 3 will receive an experimental “high-dose” regimen. Currently available safety data extends to subjects who have received the 28 mg/Kg total dose over 7 days and to another study administering 8 mg/Kg/day for 3 days (total dose 24 mg/Kg). Subjects randomized into this study’s ‘high-dose’ Arm 3 will, therefore, receive a total dose that is higher than has been previously studied in humans.

Table 7: Artesunate dosing for treatment groups 1-3.

| Treatment Group | Sample Size | Artesunate | |
| --- | --- | --- | --- |
| Dosing  mg/kg/day x 7 days | Total Dose/kg |
| 1 (Artesunate, “standard” dose) | 60 | 2 | 14 |
| 2 (Artesunate, ARC1 dose) | 30 | 4 | 28 |
| 3 (Artesunate, experimental “high” dose) | 60 | 6 | 42 |

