## Sample Size Considerations

Enrollment target for arms 1 and 3 will be 60 evaluable subjects (those completing study endpoints). Arm 2 will be used as a comparator for the 4 mg/kg study cohort tested in the study conducted in 2006. Subjects will be enrolled in the 3 groups at a ratio of 2:1:2. The dropout rate is expected to be approximately 25%. Any dropouts (e.g. withdrawals, lost-to-follow-ups etc.) will be replaced in the same arm. Therefore 190 persons may be enrolled to achieve 150 evaluable subjects. In case the enrollment target of 150 evaluable subjects cannot be met within the approved study duration an application for extension of the study duration will be filed.

Arm 2 serves as a control and will serve as a bridge to the study performed in 2006/2007. The sample size in this arm is lower as results from 60 evaluable patients are available from the earlier study conducted at the same site.

The sample size for detecting a significant difference between the 2 study arms by uncorrected Chi2-test is calculated based on an expected cure rate (i.e. early and late treatment failures) of 80% in arm 1 and 95 % in arm 3:

α 0.1

1 – β 0.8

p0 0.8

p1 0.95

Calculated sample size per arm 59

With 60 patients in arm 1 and 60 patients in arm 3 there will be a >80% chance of detecting a significant difference by uncorrected Chi2-test at a two sided 0.1 significance level. This assumes that the response rate in arm 1 is 0.8 and the response rate in arm 3 is 0.95.

Figure 1: Case sample size relative to power for α = 0.1 (Dupont and Plummer 1997)

[figure not shown]

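### The only planned cure comparison, 6 mg/kg against 2 mg/kg, tests dose dependence but cannot show that a dose above 4 mg/kg overcomes the failures seen at 4 mg/kg

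*Protocol*

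**What the plan says.** Section 3.1 sets the efficacy objective as the role of varying doses and "whether higher doses of artesunate could overcome the problem of reduced artemisinin sensitivity in the region". The Rationale section gives the principal aim the same two halves: whether failures show a trend with dose, and whether raising the dose can overcome them.

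The evidence behind the second half comes from one dose. Background Information reports: "In that study the 28-day cure rate in the 4 mg/Kg/Day X 7 days artesunate monotherapy arm (n=60) was 93.3" per cent, with 95% CI 83.8 to 98.2. The four failures, the slow clearance and the 22% still parasitaemic at 72 hours all come from that 4 mg/kg arm.

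On the arms, section 4 says "Arm 2 serves as a control and will serve as a bridge to the ARC 1 study performed in 2006/2007". Section 11.1 says "The primary outcome for the clinical part of the study will be cure rates in arms 1 and 3" and names one test of cure: "The resulting categorical frequency data between arm 1 and 3 will be compared in Chi2-tests". Section 11.2 sizes the same contrast on an "expected cure rate (i.e. early and late treatment failures) of 80% in arm 1 and 95 % in arm 3". Section 11.2 describes Arm 2 as a comparator for, and bridge to, the earlier 4 mg/kg cohort. The protocol states no cure comparison of Arm 3 with Arm 2 and no three-arm trend test. The Day 3 parasitaemia proportion is to be compared with other study sites (Secondary Outcome Measures); no comparison between arms is stated.

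**The concern.** The primary contrast starts at 2 mg/kg, below the dose at which the motivating failures were seen. A significant Arm 3 versus Arm 1 result would show that 6 mg/kg cures more patients than 2 mg/kg. It would not show whether 6 mg/kg does better than 4 mg/kg, which is the step that bears on overcoming the ARC1 failures. A trial in which 4 and 6 mg/kg perform alike could still give a positive primary test. Set against section 3.1, that result could be reported as evidence that higher doses overcome reduced sensitivity, and the Potential Benefits section expects this knowledge to inform malaria control.

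**Working it through.** **Inputs.** Section 11.2: cure 0.80 in Arm 1 and 0.95 in Arm 3, 60 evaluable per arm, uncorrected chi-square, two-sided alpha 0.10. Section 11.1: alpha 5% for comparisons between treatment groups. The two sections disagree on alpha, so both are carried through. Background Information: 56/60 = 0.933 at 4 mg/kg, Day 28. Arm 2: 30 evaluable.

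**1. The plan's own figure.** n per arm = [z(1-α/2)·√(2p̄(1-p̄)) + z(0.8)·√(p1(1-p1) + p2(1-p2))]² / (p2-p1)², with p̄ = 0.875.
= [1.645·√0.21875 + 0.8416·√0.2075]² / 0.15²
= (0.769 + 0.383)² / 0.0225 = 59.05.
The protocol states 59, so the figure reproduces. Power at 60 per arm is Φ[(0.15·√60 - 1.645·0.4677)/0.4555] = Φ(0.862) = 0.81. Exact enumeration of the two binomials gives 0.83 at alpha 0.10 and 0.73 at alpha 0.05.

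**2. The same test when 6 mg/kg only matches the 4 mg/kg result.** Take Arm 1 = 0.80 and Arm 3 = 0.933, so p̄ = 0.8667, √(2p̄(1-p̄)) = 0.4807 and √(p1(1-p1) + p2(1-p2)) = 0.4714.
- Alpha 0.10: Φ[(0.1333·√60 - 1.645·0.4807)/0.4714] = Φ(0.513) = 0.70; exact 0.71.
- Alpha 0.05: Φ[(1.0328 - 1.960·0.4807)/0.4714] = Φ(0.192) = 0.58; exact 0.58.

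**3. Dependence on the Arm 1 rate.** Exact probability of significance with Arm 3 held at 0.933 (almost all of it in favour of Arm 3):

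| True Arm 1 cure | alpha 0.10 | alpha 0.05 |
|---|---|---|
| 80% | 71% | 58% |
| 84% | 50% | 37% |
| 85% | 44% | 31% |

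The probability drops below one half once Arm 1 exceeds about 83.9% (alpha 0.10) or 81.5% (alpha 0.05).

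**4. What Arm 3 minus Arm 2 can deliver.** With 57/60 (95%) and 28/30 (93.3%) the difference is +1.7 points. The Wilson limits are 86.3 to 98.3 and 78.7 to 98.2. Newcombe 95% CI:
- lower: 1.7 - √[(95.0-86.3)² + (98.2-93.3)²] ≈ -8 points;
- upper: 1.7 + √[(98.3-95.0)² + (93.3-78.7)²] ≈ +17 points.

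Exact power for 95% versus 93.3% with 60 and 30 patients is about 6% at alpha 0.05. It is 38% for 99% versus 93.3%, and about 60% even if Arm 3 cured everyone. Adding the 60 ARC1 patients (84/90) narrows the interval to about -8 to +10 points.

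**The case against.** **The primary test is legitimate.** Section 3.1 speaks of varying and higher doses without naming 4 mg/kg as the reference, and the Rationale section puts a dose-dependent trend first. Comparing the extreme doses is an efficient way to detect dose dependence. If 2 mg/kg really is worse than 6 mg/kg, a significant result is a true positive. All of this stands, and the test should stay.

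**A reader might infer that the trial will probably succeed even if 6 mg/kg is no better than 4 mg/kg.** The documents do not settle that. It needs the 80% for Arm 1, which has no stated source. The Efficacy and Safety Profile section cites older monotherapy studies from other settings: 600 mg over 5 days gave 84% cure in Thailand, and recrudescence was 5% and 7% in China. Those rates lie at or above the point where the probability falls to one half or less.

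**A reader might also infer that 13.3 of the 15 points sized for lie below 4 mg/kg.** That mixes two planning values with one observed 56/60. Over its CI the share runs from (83.8-80)/15 = 25% to (98.2-80)/15 = 121%. The 93.3% is also a Day 28 figure, while the plan analyses Days 28 and 42 and ties 80% and 95% to neither. This argument is not relied on.

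**Nor does the label 'standard' for Arm 1 contradict Table 3.** Table 3 is a 3-day combination: 200 mg × 3 = 600 mg, or about 12 mg/kg at the 50 kg implied by 1400 mg for 28 mg/kg. Arm 1 is 14 mg/kg over 7 days as monotherapy. Section 4 puts the label in quotation marks and calls the dose relatively low.

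**A secondary pairwise estimate may sit in an analysis plan not seen here, and it cannot settle the question at this size.** Both points are fair. They do not change the fact that the protocol fixes the primary contrast and does not limit what may be concluded from it.

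**Conclusion.** The concern holds in a limited form. The only cure comparison in section 11.1 answers whether cure depends on dose between 2 and 6 mg/kg. It cannot show that going above 4 mg/kg overcomes the failures seen there. On the planned 80% for Arm 1, with 6 mg/kg merely equal to the ARC1 estimate, the test would be positive 71% of the time (alpha 0.10) or 58% (alpha 0.05), against 83% and 73% at the planned 95%. So it separates '6 beats 4' from '6 equals 4' only weakly. These sizes rest on the unsourced 80% and on a single Day 28 estimate with a wide interval. The mismatch between contrast and objective rests on neither. 'Only' refers to cure: safety and blood counts are also labelled primary and compare the dosing arms. This is a should-fix: it changes what the trial may claim and does not invalidate the primary test.

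**What to change.** In section 11.1:
- Keep the Arm 1 versus Arm 3 chi-square test, and state that it shows only whether cure depends on dose between 2 and 6 mg/kg.
- Pre-specify Arm 3 minus Arm 2 (concurrent and randomised) in cure and in Day 3 parasitaemia, each with a 95% CI, as the estimate bearing on whether higher doses overcome reduced sensitivity. Give the expected precision for cure.
- Label any version that adds ARC1 patients as supportive, non-concurrent and Day 28 only.
- State that overcoming reduced sensitivity will not be concluded from Arm 1 versus Arm 3 alone.

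The cost is a few sentences, with no new patients or data. The claim from a positive primary test becomes narrower. The Arm 3 minus Arm 2 estimate will be imprecise, about -8 to +17 points at 95% versus 93.3% with about 6% power at alpha 0.05, so it should be presented as an estimate and not as a powered test.

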### Primary Outcome Measures (Clinical Outcomes)

PCR-corrected clinical outcome will be assessed for Day 28 and 42.

Classification of clinical outcomes:

- **Adequate Clinical and Parasitological Response (ACPR)**

• Absence of parasitemia on Day 28 and 42 irrespective of temperature without previously meeting any of the criteria of Early Treatment Failure or Late Clinical Failure or Late Parasitological Failure.

- **Early Treatment Failure (ETF)**

• Development of danger signs (e.g. impaired consciousness, convulsions, respiratory distress) or severe malaria on Day 1, Day 2 or Day 3, in the presence of parasitemia

• Parasitemia on Day 2 higher than Day 0 count irrespective of temperature

• Parasitemia on Day 3 with temperature ≥ 37.5 °C

• Parasitemia on Day 3 ≥ 25 % of count on Day 0.

- **Late Treatment Failure (LTF)**
  - Late Clinical Failure (LCF)

• Development of danger signs or severe malaria after Day 3 in the presence of parasitemia, without previously meeting any of the criteria of Early Treatment Failure

• Presence of parasitemia and temperature ≥ 37.5 °C (or history of fever) on any day from Day 4 to Day 28/42 without previously meeting any of the criteria of Early Treatment Failure

- - Late Parasitological Failure (LPF)

• Presence of parasitemia on any day from Day 7 to Day 42 and temperature < 37.5 °C, without previously meeting any of the criteria of Early Treatment Failure or Late Clinical Failure

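### Cure at Day 28 and cure at Day 42 are co-equal primary outcomes, each tested at the full per-test level, with no ranking, test order or success rule, and the sample size is tied to neither day

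*Protocol*

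**What the plan says.** The Protocol Summary (Endpoints and Abstract) gives the primary clinical outcome as cure, in the sense of ACPR, on both Day 28 and Day 42. Section 8.1.1 repeats this: "PCR-corrected clinical outcome will be assessed for Day 28 and 42".

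Section 11.1 sets the analysis: "Cure rates will be analyzed separately for Day 28 and 42". On the comparison it says "The resulting categorical frequency data between arm 1 and 3 will be compared in Chi2-tests". On the level it says "The alpha level for tests used to compare differences between treatment groups will be 5" (percent). That sentence covers group comparisons generally, including the clearance-time endpoints.

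Section 11.2 sizes one arm 1 v arm 3 comparison: "This assumes that the response rate in arm 1 is 0.8 and the response rate in arm 3 is 0.95". The result is "Calculated sample size per arm 59", with power above 80% claimed at 60 per arm for "detecting a significant difference by uncorrected Chi2-test at a two sided 0.1 significance level". No day is named there. The protocol nowhere ranks the two days, orders the two tests, splits alpha, or says whether one or both must be significant.

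**The concern.** Two tests of the same dose comparison both carry primary status, and each has the full per-test level. As the text stands, a significant difference on either day could be reported as the primary finding. If so, the error rate of the primary conclusion is higher than the level of either test.

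The plan also does not say which result answers the question if one day crosses the threshold and the other does not. The sample size calculation does not help, because its single pair of cure rates is not attached to a day.

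**Working it through.** **1. The plan's own figure.** Inputs from section 11.2: cure 0.80 v 0.95, two-sided alpha 0.1, power 0.8, uncorrected chi-square. With pooled variance under the null:

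n = [1.645·√(2·0.875·0.125) + 0.842·√(0.80·0.20 + 0.95·0.05)]² / 0.15² = (0.7693 + 0.3834)² / 0.0225 = 59.05 per arm.

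The stated 59 is reproduced up to rounding. Power at 60 per arm is 80.6%, which agrees with the stated figure of above 80%. The calculation therefore covers one test at 0.1. At the 5% of section 11.1, the same 60 per arm gives 70.5%.

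**2. How the two tests are related.** Under the ACPR definition in section 8.1.1, a patient who has failed by Day 28 is also a failure at Day 42. If the same evaluable patients are used on both days, the outcomes are nested. With q28 and q42 the proportions failing by each day, the null correlation of the two test statistics is

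ρ = √[ q28(1 − q42) / (q42(1 − q28)) ].

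Example: q28 = 0.10, q42 = 0.20 gives ρ = √(0.08/0.18) = 0.67.

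**3. Chance that at least one test is significant when dose has no effect.** This is 1 − P(|Z₁| < c and |Z₂| < c) for a bivariate normal with correlation ρ, where c = 1.960 at 5% and 1.645 at 0.1. Section 11.1 does not state sidedness; two-sided is assumed. Independent tests set the ceiling: 1 − 0.95² = 9.75%, and 1 − 0.90² = 19%. If every failure is seen by Day 28, the tests are identical and there is no inflation.

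The share of failures seen by Day 28 is not in the protocol, so it is varied here, with 20% failing by Day 42:

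| Share seen by Day 28 | ρ | Either test, 5% each | Either test, 0.1 each |
|---|---|---|---|
| 25% | 0.46 | 9.2% | 17.8% |
| 50% | 0.67 | 8.5% | 16.4% |
| 70% | 0.81 | 7.8% | 15.0% |
| 80% | 0.87 | 7.3% | 14.1% |
| 90% | 0.94 | 6.6% | 12.9% |
| 95% | 0.97 | 6.2% | 12.1% |

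**4. Check by simulation.** Uncorrected chi-square, 60 v 60, nested failures, equal rates in both arms, 1,000,000 trials per setting, 5% per test:

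| Failing by Day 28 / Day 42 | Either test significant |
|---|---|
| 5% / 20% | 8.9% |
| 10% / 20% | about 8.5% |
| 18% / 20% | 6.5% |
| 19% / 20% | 6.0% |
| 6.7% / 7.4% | 6.1% |

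The 6.7% in the last row comes from the 93.3% 28-day cure rate quoted for ARC1; its Day 42 value is assumed. With only 5% failing by Day 42 and 50% to 90% of failures seen by Day 28, the figure is 5.7% to 6.7%, because the test is conservative at such low counts. At 0.1 the uncorrected test can itself run above nominal (about 12% with 5% failing), so the 19% ceiling is approximate.

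**5. Which day the sample size describes.** If any failure occurs after Day 28, cure at Day 42 is lower than at Day 28, and one pair of rates cannot fit both days. Suppose 80% v 95% refers to Day 42 and 70% of failures in each arm are seen by Day 28. Day 28 cure is then 1 − 0.7·0.20 = 86% v 1 − 0.7·0.05 = 96.5%. Power at 60 per arm and two-sided 0.1 is Φ[(0.105·√60 − 1.645·√(2·0.9125·0.0875)) / √(0.86·0.14 + 0.965·0.035)] = Φ(0.40) = 65%, not 80.6%.

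**The case against.** **The 5% is a per-test level.** This is correct. A reader might infer that the protocol promises an overall 5% and breaks that promise. It does not: section 11.1 sets a level for tests and makes no claim about an overall error rate.

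**No passage says that a win on either day is enough.** This is also correct. If both days had to be significant, the error could not exceed the level of one test. The ACPR definition, which names both days together, could be read that way. But section 11.1 calls for separate analyses, and under nesting a joint outcome is simply Day 42 cure, which would leave the Day 28 test without a purpose. The success rule is therefore open, and the inflation is conditional on the either-day reading.

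**Most failures may come early.** The protocol describes a half-life under one hour and no activity beyond 12 hours after an oral dose, so drug does not persist to delay recrudescence. PCR correction also removes later reinfections. This supports the lower end of the range, near 6%. It does not bring the inflation to zero: the plan takes smears on Days 35 and 42 and counts failures to Day 42. The quoted ARC1 results stop at 28 days and cannot settle the matter.

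**An analysis plan may set a test order, and both cure rates will be reported with confidence intervals.** Both points soften the consequence. The choice of primary outcome and the sample size are nevertheless fixed in this protocol, and it fixes two primaries and one unattached sample size.

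**Conclusion.** The point holds as a defect of structure: two co-equal primary time points, a full-level test at each, no rule linking them, and a sample size tied to neither.

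Its numerical size is conditional. If success on either day counts, the false-positive chance is about 6% to 9% at 5% per test, at most about 9.75%. At 0.1 per test it is roughly 12% to 19%. These figures assume nested outcomes in the same patients, two-sided tests and an assumed share of failures by Day 28.

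A reader might take a single value, such as 8.5%, as the trial's error rate. The documents do not support that, because they give neither the timing of failures nor the success rule, and sections 11.1 and 11.2 disagree on alpha for the same comparison. The defect should be corrected but is not fatal to the trial.

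**What to change.** In section 11.1, name one day as the single primary test. Make the other day key secondary, or test it at the same level only if the first is significant. Which day comes first is the sponsor's choice: Day 42 uses the full follow-up, while Day 28 matches the efficacy rule under Cohort Halting Rules and the ARC1 results. In section 11.2, state which day the 80% v 95% assumption describes.

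Either version keeps the error at the chosen alpha with a sentence or two and no added patients. The only loss is the freedom to claim the second day alone. A Bonferroni split of 5% would cost more: at 2.5% per test, power is 59.8% with 60 per arm, and 80% power needs 92 per arm.

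Separately, give one alpha in both sections. Keeping 0.1 leaves the sample size as it is. Keeping 5% means accepting 70.5% power at 60 per arm, or enrolling 76 evaluable patients per arm for 80%. That cost comes from the conflict between the two levels, not from naming a primary day.

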Once it develops and spreads, resistance to artemisinin derivatives, currently the most essential antimalarial drugs for the treatment of *Plasmodium falciparum* malaria, could very well be the most devastating event in the history of malaria control in the 21st century (Noedl 2005). Forty countries have officially adopted artemisinin-based combination therapy (ACT) for the treatment of malaria since 2001. Twenty alone have adopted the combination of artemether and lumefantrine as their first- or second-line treatment for *P. falciparum* malaria. Artemisinin and its derivatives are the most potent and rapidly acting antimalarial drugs. They reduce the infecting malaria parasite biomass by roughly 104 per cycle (White et al. 1999).

Currently used ACTs are starting to fail on both sides of the Cambodian-Thai border. In a recent study the efficacy of the combination of artesunate and mefloquine was reduced to only 79.3% with a 42-day follow-up in Pailin Province, in close proximity to our study site (Denis et al. 2006). Recent reports also suggest increasing numbers of failures with artemisinin combination therapies along the eastern borders of Thailand (Trat Province – data not PCR corrected), potentially due to artemisinin resistance (Vijaykadga et al. 2006). The authors report 21.4% failures in Trat Province with M5AS, a combination of 25 mg/kg mefloquine and 12 mg/kg of oral artesunate (as compared to only 3.4% in Tak province, along the Thai-Myanmar border, an area that is infamous for its high levels of drug resistance).

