## Inclusion Criteria

Male and female subjects with a diagnosis of acute falciparum malaria meeting all criteria listed below may be included in the study:

1. Acute symptomatic falciparum malaria infection as determined by malaria smear with a parasite density of 1000 to 200,000 asexual parasites/L as determined on the thick/thin screening smear with fever (defined as ≥37.5ºC), or reported history of fever within the last 48 hours.
2. Age: 18-65 years old
3. All females between the age of 18 and 50 are required to have a negative human chorionic gonadotropin (hCG) pregnancy test (urine). All females of childbearing potential (not surgically sterile, or less than two years menopausal) are required to use an acceptable method of contraception, such as implant, injectable, or oral contraceptive(s), if possible with additional barrier contraception, intrauterine device, sexual abstinence, or vasectomized partner, throughout the study.
4. Written informed consent obtained
5. Willing to stay under close medical supervision for the study duration of 42 days
6. Otherwise healthy Out-patients

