## Exclusion Criteria

Subjects presenting with any of the following will not be included in the study:

1. Pregnant women, nursing mothers, or women of childbearing potential who do not use an acceptable method of contraception (as described in Inclusion Criteria, #3)
2. Mixed malaria infection on admission by malaria smear
3. A previous history of intolerance or hypersensitivity to the study drug artesunate or to drugs with similar chemical structures, such as artemether, artemisinin or dihydroartemisinin
4. History of malaria drug therapy administered in the past 30 days
5. Previous participation in this trial, or participation in any other studies involving investigational or marketed products, concomitantly or within 30 days prior to entry in the study
6. History of significant cardiovascular, liver or renal functional abnormality or any other clinically significant illness, which in the opinion of the investigator would place them at increased risk.
7. Symptoms of severe vomiting (no food or inability to take food during the previous 8 hours).
8. Signs or symptoms of severe malaria (adapted from WHO recommendations (2003): prostration, impaired consciousness, respiratory distress, convulsions, systolic blood pressure < 70 mm Hg, abnormal bleeding, severe anemia with hemoglobin <8 g/dL or HCT <24%, hyperparasitemia at >4% parasitized red blood cells).
9. Unable and/or unlikely to comprehend and/or follow the protocol

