## Randomization Procedures

Subjects will be assigned unique identification codes (ARC08 followed by a 3 digit number) in order of inclusion and randomly assigned to either one of the artesunate groups. The ratio of enrollment into the three groups is 2:1:2. Randomization will not be stratified and will be done using random number tables in blocks of 10. A randomization list will be created prior to beginning the trial. Sealed individual envelopes that will be opened only on enrollment of each subject will be used. The study personnel enrolling the subject will therefore not know which group the patient will be assigned to until opening the envelope.

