## Laboratory Evaluations

### Laboratory Evaluations/Assays

- Hematology (hematocrit, RBCs, WBCs, platelets) on days 0, 3, 6, and 14 (or whenever clinically warranted) (2 ml per blood draw).
- Glucose on days 0 (or whenever clinically warranted) (2 drops per blood draw).
- ALT on days 0, 3, 6, and 14 (or whenever clinically warranted) (1 ml per blood draw)
- Urine pregnancy test: Urine beta-HCG test. All female subjects will undergo a pregnancy test at baseline. Pregnant women will not be eligible for entry into the study.
- Urine (approximately 5ml) will also be collected from all participants to be frozen for probable antimalarial drug screening on the day 0 sample at a later date.
- Peripheral blood smears up to 8 times on Day 0 from blood drawn for other reasons or by finger prick blood smear at 12 and 18 hours and then 4 times daily until negative on 2 successive occasions. Thereafter blood smears will be performed on Days 14, 21, 28, 35, and 42 :
  - To determine species of parasite
  - To quantify parasitemia

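### The primary arm 1 v arm 3 cure test is valid but ignores admission parasite density; prespecifying one adjustment for it would gain a little power at almost no cost

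*Protocol*

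**What the plan says.** Section 11.1 makes cure in arms 1 and 3 the primary outcome, analysed separately at Day 28 and Day 42. It describes each arm by "Cure rates will be summarized along with 95% confidence intervals (exact based on binomial distribution" and fixes the comparison: "The resulting categorical frequency data between arm 1 and 3 will be compared in Chi2-tests". No covariate is named. Section 11.2 sizes the trial on the same uncorrected chi-square.

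Section 5.5 states: "Randomization will not be stratified and will be done using random number tables in blocks of 10". Section 5.3 admits patients "with a parasite density of 1000 to 200,000 asexual parasites" per microlitre (the micro sign is lost in the extracted text). Section 5.4 also excludes "hyperparasitemia at >4% parasitized red blood cells". Section 6.2.1 gives as one purpose of the smears "To quantify parasitemia", and Appendix A schedules a smear at hour 0. Each final count is the geometric mean of two readings by microscopists blinded to treatment.

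On mechanism, Background Information says that artemisinins "reduce the infecting malaria parasite biomass by roughly 104 per cycle" (10 to the power 4; the superscript is lost). It adds that their effect depends on how many parasite generations are exposed.

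**The concern.** All arms are treated for the same 7 days. If each cycle removes a roughly fixed fraction of parasites, a patient who starts with more of them has less margin for cure at the same dose. Part of the primary outcome also depends on absolute clearance. Under section 8.1.1, any parasitemia on Day 3 with a temperature of at least 37.5 °C is an early failure, whatever the starting count. (The other Day 3 count criterion, 25% or more of the Day 0 count, scales with the starting count and does not carry this argument.) In the earlier trial at this site, 22% of the artesunate arm were still parasitemic at 72 hours.

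A baseline value of this kind can be used to sharpen the arm comparison. About 15 failures are expected in the two arms (60 × 0.20 + 60 × 0.05 = 12 + 3), so there is little power to spare. At stake is a small loss of efficiency and some avoidable noise in the estimated dose effect.

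**Working it through.** **The plan's own figure.** Inputs from section 11.2: cure 0.80 v 0.95, power 0.80, two-sided alpha 0.10. With mean cure 0.875,

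n = [1.645 × √(2 × 0.875 × 0.125) + 0.842 × √(0.80 × 0.20 + 0.95 × 0.05)]² / 0.15² = 59.05 per arm.

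The stated 59 is reproduced. With 60 per arm the formula gives 80.6% power at 0.10 and 70.5% at the 5% level named in section 11.1. Exact binomial power is 83.0% and 73.0%. The conflict between the two alpha levels is a separate matter; both are carried below.

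**How density could matter.** log10(200,000 / 1,000) = 2.30. At 4 log10 per 48-hour cycle this is 2.30 / 4 × 48 = 27.6 hours of treatment out of 168. The window may be slightly narrower: at the earlier trial's Day 0 mean of 4.31 million red cells per microlitre (Table 2.1, artesunate arm), the 4% exclusion falls at 0.04 × 4,310,000 = 172,400 per microlitre.

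**Power.** Simulation with 60 per arm and marginal cure 80% v 95%. Assumptions not in the protocol: log10 density uniform over the eligibility window (SD 0.66), and the odds ratio (OR) of failure per 10-fold density as listed. 5,000 trials per row; Monte Carlo standard error about 0.6 point per figure at 5%, with both tests run on the same simulated trials.

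| Assumed OR | 5%: chi-square | 5%: adjusted score | 10%: chi-square | 10%: adjusted score |
|---|---|---|---|---|
| 1 | 73.1% | 73.2% | 82.7% | 82.9% |
| 1.5 | 71.7% | 72.4% | 82.3% | 82.7% |
| 2 | 73.4% | 74.3% | 82.9% | 83.7% |
| 3 | 72.9% | 75.3% | 83.5% | 84.5% |
| 5 | 73.2% | 77.2% | 82.8% | 85.9% |

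A narrower assumed spread (SD 0.52, truncated to log10 3 to 5.3; 4,000 trials, 5% level) gave 72% v 72% at OR 1, 72% v 73% at OR 2, 72% v 75% at OR 3 and 73% v 76% at OR 5.

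In patients, by the power formula at 5% (60 per arm 70.5%, 61 71.2%, 62 71.9%, 63 72.6%, 64 73.3%, 66 74.6%), the gains in the table are worth about 2 per arm at OR 2, 4 at OR 3 and 6 at OR 5.

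**Type I error.** With equal cure of 87.5% in both arms, at nominal 5%, the chi-square rejected in 4.5 to 5.2% of trials and the adjusted score test in 5.1 to 5.5%. Further runs of the adjusted analysis stayed within 4.6 to 6.2%.

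**Chance imbalance.** The standard error of the arm difference in mean log10 density is 0.664 × √(2/60) = 0.121. The 95% limit is 1.96 × 0.121 = 0.2375, a 1.7-fold ratio of geometric means. The resulting shift in the cure difference is about ln(OR) × 0.2375 × 0.875 × 0.125, which is 1.8 points at OR 2, 2.9 at OR 3 and 4.2 at OR 5. The planned difference is 15 points, and its ordinary 95% half-width is 1.96 × √[(0.16 + 0.0475)/60] = 11.5 points.

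**The case against.** The strongest objection is that the premise is not established. A reader might infer that density is a known, strong predictor of cure. The documents do not say so: where the protocol discusses failures, it links them to long parasite clearance, high IC50 and inadequate drug levels. The mechanism alone does not settle it. At 4 log10 per cycle, 7 days give 168 / 48 × 4 = 14 log10 of killing, while 200,000 per microlitre in 5 litres of blood (an assumed volume) is about 10^12 parasites. At the cited rate even the top of the window clears. Density can decide cure only where killing is slower than cited. Reduced sensitivity is the trial's own premise, but the protocol does not quantify it. This objection stands, and it is why the effect is shown over a range that includes no effect.

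A reader might also infer that chance imbalance biases the result. It does not. Imbalance is part of the sampling error that the chi-square already covers, and the simulated error rate confirms this. Nor is 200-fold an observed spread; it is the eligibility window.

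Two practical objections carry some weight. The unadjusted test matches the sample size calculation, and raw cure rates compare directly with the earlier trial's 93.3%, to which arm 2 is the bridge. Keeping the raw results as support answers both. An analysis plan that is not shown might add an adjusted analysis, but the primary test is already fixed in the protocol.

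**Conclusion.** The point holds as a minor efficiency improvement. It is not an error: the chi-square is valid and nothing in the plan is contradicted. At two-sided 5%, adjustment is worth about 1 point of power at an assumed OR of 2, 2 to 3 points at OR 3, 3 to 4 points at OR 5, and nothing is lost at OR 1. At the 0.10 level used for sizing, the gain is 1 point or less up to OR 3 and about 3 points at OR 5. These sizes rest on assumed odds ratios and assumed density distributions. It would be wrong to conclude that the trial is seriously underpowered for want of this covariate; testing at 5% rather than 0.10 costs about 10 points (80.6% v 70.5%), far more. The case for acting is that the change is nearly free and must be made in advance: in an open-label trial, an adjustment chosen after an imbalance has been seen carries less weight.

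**What to change.** In section 11.1, define the primary arm 1 v arm 3 cure test as a score test for arm from a logistic model containing arm and log10 admission density, with no other covariate. Name the density as the pre-dose hour 0 count, since Day 0 has up to eight smears. Report the cure difference standardised over the observed densities with its 95% confidence interval. Keep the raw cure proportions with exact intervals and the unadjusted chi-square as supporting results, so that comparison with the earlier trial is preserved. Leave out a density-stratified test, because the protocol offers no cut-points.

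The score test needs only the model without arm, so it still works if arm 3 has no failures. Under the plan's assumptions the chance of that is 0.95^60 = 4.6%. State in advance which interval for the difference will be reported in that case.

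The cost is a few sentences of analysis wording. No new data, visits or patients are needed, and one covariate is supportable with about 15 expected failures.
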